Currently, studies found that PI can be used to evaluate the effect of nerve block primarily focused on awake adults [16, 17]. Xu Z reported that PI provides an earlier and more sensitive indicator to assess the onset of caudal block under ketamine anesthesia [18]. Still, there is a lack of relevant research on the effect of peripheral nerve block in children. The supraclavicular brachial plexus block (SCB) can be used for surgical anesthesia and analgesia of the upper arm, elbow, forearm, wrist, and hand below the shoulder joint. Therefore, the aim of this study is to evaluate the effect of PI on predicting the success of SCB in children under general anesthesia with sevoflurane and propofol.

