### Outcomes

#### Primary outcome

The primary outcome is to assess the effects of PI on the success of supraclavicular brachial plexus block in pediatric patients under sevoflurane or propofol general anesthesia. PI values of the index finger and little finger will be recorded before induction of general anesthesia in the operating room, immediately after laryngeal mask placement, 5 min, 10 min, 15 min after SCB, immediately after surgery, after removal of laryngeal mask when the child is awake and in PACU. Record the dosages of opioids and vasoactive drugs during the operation. Evaluate the complications and recovery quality in children. (1) Assessment of restlessness and delirium during the recovery period and 30 min in PACU. (2) Postoperative pain score. Postoperative complications: nausea and vomiting, neurological dysfunction, Horner syndrome, respiratory depression, etc.

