### Block effect evaluation

Complete block: There is no significant fluctuation of the HR, BP, and RR during the operation (heart rate and blood pressure increased by less than 10% compared with the baseline value, and respiratory rate increased by less than 20%). Partial block: When a non-single nerve innervates the surgical site, there is a specific innervated area that causes HR, BP, and RR fluctuations (HR, BP increase ≥ 10% from the baseline value, RR increase ≥ 20%), while there is no significant fluctuation in operation in other innervated area. Block failure: Operation in any innervated area caused substantial changes in HR, BP, and RR. For partial block and failure of block, a single dose of sufentanil (0.01 μg/kg) and a pump of 0.1–0.2 μg/kg/min remifentanil for supplementary analgesia.

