### Data collection and management

Record the PI values of the index finger and little finger on blocked and non-blocked sides in all children. Data collection and completion will be carried out by two research assistants blinded to the grouping of subjects. The clinical trial supervisors will periodically review the quality of data entry to ensure the authenticity and reliability of the program. This data supervision committee has no conflict of interest in the study. All information related to the study will be stored securely.

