The pediatric nerve block is mainly performed under sedation or general anesthesia [21, 22]. Sevoflurane and propofol are commonly used for induction and maintenance of general anesthesia in children [23, 24], but both have a vasodilator effect. Sebastiani Anne found that PI values of the two limbs were not significantly different but relatively higher than baseline values after 25 min of intermuscular sulcus block and sevoflurane inhaled for maintenance. Sevoflurane is considered to increase PI value by increasing blood flow of the muscle tissue on the unblocked side, and the PI value of the blocked side does not increase, which means that vasodilatation has reached the maximum after nerve block [19]. Park SG et al. found that the PI value increased after propofol anesthesia induction and sevoflurane anesthesia maintenance in patients without regional block [25]. Both propofol and sevoflurane general anesthesia affects the PI value. There is still no study about PI changes after brachial plexus nerve block after sevoflurane or propofol anesthesia induction in children. We speculate that the changes of PI after brachial plexus block may exist in different periods after the administration of sevoflurane or propofol. For example, when the vasodilator effect of propofol reaches its peak, the PI may have increased to the highest value. At this time, PI may not increase further after nerve block. However, PI values will change differently following the metabolism of anesthetics on the blocked and non-blocked sides. Moreover, the surgery for upper limb fractures could always be completed in about 1 h in children. And anesthesia and analgesia effect last 6–8 h after nerve block with ropivacaine. We will monitor the PI values of both sides after nerve block at the beginning and the end of the surgery. The influence of general anesthetics on PI values will be excluded after children wake up.

In conclusion, we intend to evaluate the prediction effect of PI on supraclavicular brachial plexus block after the induction of general anesthesia with sevoflurane or propofol in children, which could be used as a clue to evaluating the requirements of postoperative analgesics in children.

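### The primary outcome ranks none of its ten or twelve post-block PI readings first, and the readings after surgery cannot predict a block grade already given

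*Protocol article*

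**What the plan says.** The Introduction states the aim as prediction: to "evaluate the effect of PI on predicting the success of SCB in children under general anesthesia with sevoflurane and propofol". The Primary outcome section reads: "The primary outcome is to assess the effects of PI on the success of supraclavicular brachial plexus block in pediatric patients under sevoflurane or propofol". It then lists the readings. "PI values of the index finger and little finger will be recorded before induction of general anesthesia in the operating room", again after mask placement, and then "5 min, 10 min, 15 min after SCB, immediately after surgery, after removal of laryngeal mask when the child is awake and in PACU". Data collection and management adds the side: "Record the PI values of the index finger and little finger on blocked and non-blocked sides in all children". None of these is singled out. The only PI measure tied to one time is the PI ratio at 10 min, listed under Secondary outcomes without naming a finger.

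Block effect evaluation grades the block from vital signs in surgery. A complete block is defined by "There is no significant fluctuation of the HR, BP, and RR during the operation". Supplementary opioids depend on that grade: "For partial block and failure of block, a single dose of sufentanil" and a remifentanil infusion.

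Statistical analyses lists general two-group tests and a logistic model with stepwise selection of variables. It names no primary PI test. In Sample size, the bold cell of Table 1 is 37 + 10 at alpha 0.05 and beta 0.10, giving 47 and then 52 per group.

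**The concern.** Two separate matters arise.

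**No primary measure.** Two fingers and up to six post-block times give up to twelve candidate readings per arm, before the second side, the choice between increment and ratio, and the second arm are counted. Stepwise selection would itself choose among them on the data. The sample size allows for one test. A trial that can call PI predictive on any one of these readings has a higher false-positive rate than the design implies, and an optimistic accuracy for whichever reading looks best.

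**Order of events.** The readings at the end of surgery, on waking and in PACU come after the block has been graded and after opioids have gone to the partial and failed blocks. Left unranked inside the primary outcome, they could enter the prediction analysis although they follow what they would be predicting.

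**Working it through.** **1. The plan's own figure.** Table 1 does not state its effect size. Take one ROC curve tested against AUC 0.50, two-sided, with a 4:1 case mix (the article's insufficiency rate below 20%) and an assumed AUC of 0.80. The Hanley–McNeil standard errors at 37 + 10 are 0.1040 under the null and 0.0690 under the alternative. The condition is

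z(1−α/2) × SE₀ + z(1−β) × SE₁ ≤ 0.80 − 0.50

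1.960 × 0.1040 + 1.282 × 0.0690 = 0.2038 + 0.0884 = 0.292 ≤ 0.30, so 37 + 10 suffices. A search at an exact 4:1 ratio gives 38 + 10, and in all 16 cells of the table the larger group differs by exactly 1. Then 47 × 1.10 = 51.7, rounded up to 52, and 2 × 52 = 104. Table 1 is therefore consistent with one ROC test per arm at alpha 0.05.

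**2. Counting the readings.**
- 5, 10 and 15 min: 2 fingers × 3 times = 6.
- All post-block times: 2 × 6 = 12, or 2 × 5 = 10 if awake and PACU are one time.

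**3. Chance of at least one nominal p < 0.05 per arm when PI carries no information.** For independent readings this is 1 − 0.95^k: 26.5% for k = 6, 40.1% for k = 10 and 46.0% for k = 12. PI readings on one child will be correlated, so these are upper figures. The table assumes the same correlation r between fingers and between times, and r² where both differ. It gives simulated rank-sum tests on 37 v 10 children, with the normal approximation in brackets where it was also run.

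| r | 6 early readings | 10 readings | 12 readings |
|---|---|---|---|
| 0.5 | 22% (22%) | 32% | 35% (35%) |
| 0.7 | 18% (18%) | 24% | 27% (26%) |
| 0.8 | 15% (15%) | 20% | 22% (21%) |
| 0.9 | 12% (12%) | 14% | 16% (15%) |

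A separate run of 4,000 gave 35.7% for twelve readings at r = 0.5, hence an upper end of 36%. A single reading gives 5%. When the true AUC is 0.50, the mean of the best AUC is 0.58–0.60 for six readings and 0.61–0.63 for twelve at r of 0.5–0.7. At r = 0.9 it is 0.55 and 0.56.

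**4. What the sample can carry.** Power at 37 + 10 is Φ[(0.30 − z × 0.1040) / 0.0690].
- One test, α = 0.05: (0.30 − 0.2038) / 0.0690 = 1.39, power 92%.
- Bonferroni over 6, α = 0.0083: (0.30 − 2.638 × 0.1040) / 0.0690 = 0.37, power about 65%.
- Bonferroni over 12, α = 0.0042: (0.30 − 2.865 × 0.1040) / 0.0690 = 0.03, power about 51%.

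**5. Sequence.** The order is SCB, the 5, 10 and 15 min readings, grading during surgery, opioids for partial and failed blocks, and then the end-of-surgery, awake and PACU readings. The last two or three times follow both the grade and the opioids. The article does not fix incision relative to 15 min, so that reading may also overlap the grading.

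**The case against.** **The late readings have their own purpose.** The abstract and the Discussion say that PI on the two sides after waking may help to judge the block without the anesthetic, with a block lasting 6–8 h. This stands. A reader might infer that the whole primary outcome is a look-back. The documents do not support that: the early readings can predict, and the late ones answer a different, legitimate question. What remains is that the primary outcome does not separate the two.

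**Rescue opioids.** A reader might infer that these drugs make late PI look more discriminating. No section gives any effect of sufentanil or remifentanil on PI. The non-blocked side is also recorded, and may share systemic drug effects. Nor does the Discussion claim that waking removes all confounding. It says only: "The influence of general anesthetics on PI values will be excluded after children wake up".

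**Selective reporting.** A reader might infer that the best AUC will be the one reported. The article names no ROC analysis and promises no such search, and multiplicity rules are often left to an analysis plan. This is fair. Even so, which variable at which time is primary belongs in the protocol, and the text as written leaves it open.

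**Assumed correlations.** True. At 0.9 the error rate is still two to three times nominal.

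**Other outcomes in the same paragraph.** Opioid dose, delirium, pain and complications also appear under Primary outcome. The abstract confines the primary outcome to PI and block success, so this is layout rather than a further multiplicity problem.

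**Conclusion.** The point holds in a limited form. The primary outcome lists ten or twelve post-block PI readings per arm without ranking them, against a sample size consistent with one test. If each may be tested, the false-positive chance per arm is about 12–22% for the six early readings and about 15–36% for all twelve. These figures rest on assumed correlations of 0.5–0.9 and on testing every reading, which the article neither plans nor rules out. The power figures rest on an AUC of 0.80 solved back from Table 1.

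That the post-surgery readings cannot predict the intra-operative grade follows from the article's own order of events and needs no assumption. The documents do not show that opioids bias those readings.

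**What to change.** - Name one primary predictor per arm from the measures already recorded. An example is the blocked-side PI ratio at 10 min after SCB, at one pre-specified finger. The little finger fits the ulnar focus of the aim and the sample size. Because the grade depends on the nerves supplying the surgical site, the sponsor should justify the choice.
- State how alpha is handled across the arms. Two independent tests at 0.05 give 1 − 0.95² = 9.75%. Splitting to 0.025 per arm gives (0.30 − 2.241 × 0.1040) / 0.0690 = 0.97, power about 83% at 37 + 10. Treating the arms as two separate questions, each at 0.05, is the alternative and should be stated.
- Make the other finger and the 5 and 15 min readings secondary, with Holm adjustment.
- Admit to the prediction analysis only readings taken before the block is graded, and say how a 15 min reading after incision is treated.
- Report the end-of-surgery, awake and PACU readings as a separate secondary or descriptive analysis of the question in the Discussion.

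No measurement is added or lost. The cost is that the sponsor commits to one finger and one time, plus any power given up by splitting alpha. Recruitment was planned to end in December 2022, so the choice should be dated and made before PI is examined against block grade.

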#### Secondary outcomes

The secondary outcome includes mean arterial blood pressure (MAP), heart rate (HR), and PI ratio (correlation between baseline PI and 10min after SCB). The age, gender, ASA classification, BMI, anesthesia time, operation time, anesthesia recovery time, duration of stay in PACU, and duration of postoperative hospital stay will be recorded.

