**Methods/design:**

This is a mono-center, parallel, 2-arm randomized superiority trial. One hundred four children aged 1 month to 12 years who undergo upper limb surgery will be enrolled in this study. According to anesthesia induction and maintenance medication, they will be divided into sevoflurane and propofol groups. The PI values of the index and little finger will be recorded on the blocked and non-blocked sides of supraclavicular brachial plexus block (SCB) in all children. The primary outcome is to assess the effects of PI on the success of supraclavicular brachial plexus block in pediatric patients under sevoflurane or propofol general anesthesia. The secondary outcome includes mean arterial blood pressure (MAP), heart rate (HR), and correlation between baseline PI and 10 min after SCB (PI ratio).

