### Sample size

According to literature reports [15], the probability of ulnar nerve insufficiency is less than 20%; the sample size is calculated: As shown in Table 1, the preliminary estimated sample size is 47 cases, and the withdrawal rate is assumed to be 10%. The calculation is 52 cases per group, so 104 children will be included in this experiment.

**Table 1 Tab1:** Sample size estimation results

		Type I Error- Alpha			
		0.20	0.10	0.05	0.01
Type II Error -Beta	0.20	16 + 4	23 + 6	30 + 8	46 + 12
	0.10	21 + 6	29 + 8	**37 + 10**	54 + 14
	0.05	26 + 7	35 + 9	43 + 11	62 + 16
	0.01	37 + 10	47 + 12	57 + 15	78 + 20

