## Discussion

PI has been used to evaluate the effect of brachial plexus, sciatic nerve, stellate ganglion in adults, and sacral canal block in children [18–20]. Sebastiani Anne et al. reported that PI increased in successful intermuscular sulcus nerve block, which can be used as an indicator of successful block in conscious patients [19]. Abdelnasser A et al. studied 77 adult patients undergoing elective orthopedic surgery via ultrasound-guided supraclavicular brachial plexus block. They found that the PI value of the blocked limb increased compared with the baseline value, and the ratio of PI values was higher than that of the limbs on the unblocked side at all time points. In addition, when the PI increment and PI ratio are 3.3 and 1.4 respectively at 10 min after injection as the limit to determine the success of the block, both the sensitivity and specificity for the success of the block were 100% [15]. When PI is used to evaluate the effect of sacral canal block under ketamine anesthesia in children, it is an earlier, more objective, and sensitive indicator than acupuncture sensation and cremasteric reflex [18]. However, the studies mentioned above have certain limitations. The effect of nerve block is not all-or-none. Abdelnasser A et al. did not analyze the cases of block failure and did not record the changes in PI values of partial block [15]. Since the brachial plexus is a cluster of nerves, some nerves are relatively difficult to block with different blocking methods. Therefore, a suitable evaluation method should be able to accurately assess the block's complete, partial, and failure.

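### The secondary outcome PI ratio is defined as a correlation with an unnamed baseline, so as written it cannot show a block effect or classify a child

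*Protocol article*

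**What the plan says.** Under Secondary outcomes, the protocol article lists the "PI ratio (correlation between baseline PI and 10min after SCB". The abstract gives the same definition: "correlation between baseline PI and 10 min after SCB (PI ratio". Neither place says which reading is the PI baseline, and no other section does.

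The Primary outcome section schedules PI readings "before induction of general anesthesia in the operating room, immediately after laryngeal mask placement, 5 min, 10 min, 15 min after SCB", followed by readings at the end of surgery, on waking and in PACU. Two of these precede the block, and induction of anaesthesia lies between them.

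The Discussion bears on the definition in two places. It reports an adult supraclavicular study in which block success was judged "when the PI increment and PI ratio are 3.3 and 1.4 respectively at 10 min after injection". It also states that "Both propofol and sevoflurane general anesthesia affects the PI value".

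Under Data collection and management the instruction is: "Record the PI values of the index finger and little finger on blocked and non-blocked sides in all children".

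**The concern.** The name of the outcome and its definition describe different quantities. A ratio of two readings is a value for each child and can be set against block status. A correlation belongs to a group of children and describes how closely two readings line up, not how far one has moved from the other. The trial asks whether PI can tell complete, partial and failed blocks apart, and for that only the first kind of quantity is of use. The article fixes the outcome and fixes it wrongly, so this is more than detail left to a fuller document.

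If the word is corrected to a quotient, its denominator is still open. The two candidate readings are separated by an event that, on the article's own account, changes PI. The choice therefore decides whether the ratio measures the block, or the block and the anaesthetic together. If it is left open, it could also be made after the data have been seen.

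**Working it through.** The documents attach no figure to this outcome, so there is none to reproduce, and the sample size does not depend on it.

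**1. A correlation ignores a common rise.** For any c > 0, corr(x, c·x) = 1. Take three children with baseline PI 1, 2 and 3. If nothing changes, the 10-minute values are 1, 2, 3 and the correlation is 1. If PI doubles in every child, they are 2, 4, 6 and the correlation is again 1. The quotient is 1.0 in every child in the first case and 2.0 in the second.

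**2. It is not the quantity cited.** A correlation lies between −1 and 1. A cut-off of 1.4, applied to decide whether a patient's block succeeded, is outside that range. The Discussion must therefore mean a per-patient ratio.

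**3. The denominator matters.** For one child,

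PI(10 min) / PI(pre-induction) = [PI(post-mask) / PI(pre-induction)] × [PI(10 min) / PI(post-mask)].

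The first factor is the change over induction. The second is the change after the block, plus any later drift. Assumed example of a failed block: PI 2 before induction, 4 after the mask, 4 at 10 minutes. The ratio is 4/2 = 2.0 on the first baseline and 4/4 = 1.0 on the second.

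**4. Illustration under assumed inputs.** The documents give no size for the anaesthetic effect, so a range is used:
- pre-induction PI log-normal, median 2, log-SD 0.5;
- 80% successful blocks (the Sample size section puts ulnar insufficiency below 20%);
- a successful block multiplies PI by 1.4, with noise log-SD 0.15 at 10 minutes;
- the anaesthetic multiplies PI by 1.0 to 3.0, with between-child log-SD 0.3 or 0.5 (none at 1.0);
- reading noise of log-SD 0.1 on the post-mask value only, and no drift after it.

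Pairs in the table are for log-SD 0.3 / 0.5.

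| Anaesthetic multiplier | Correlation, pre-induction with 10 min (same in successes and failures) | Failures above 1.4, pre-induction baseline | AUC, pre-induction | Failures above 1.4, post-mask baseline | AUC, post-mask |
|---|---|---|---|---|---|
| 1.0 | 0.95 | 1% | 0.94 | 3% | 0.91 |
| 1.5 | 0.81 / 0.64 | 58% / 55% | 0.762 / 0.675 | 3% | 0.91 |
| 2.0 | 0.81 / 0.64 | 86% / 75% | 0.761 / 0.675 | 3% | 0.91 |
| 3.0 | 0.81 / 0.64 | 99% / 93% | 0.763 / 0.674 | 3% | 0.91 |

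One cell by hand (multiplier 2.0, log-SD 0.3): the SD of the log ratio is √(0.3² + 0.15²) = 0.335. The share of failures above 1.4 is Φ[(ln 2 − ln 1.4)/0.335] = Φ(1.06) = 0.86. The AUC is Φ[ln 1.4/(√2 × 0.335)] = Φ(0.71) = 0.76.

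The correlation does not distinguish successes from failures in any row. The multiplier cancels from the AUC. What lowers the AUC on the pre-induction baseline is the spread of the anaesthetic effect between children; the multiplier moves only the share beyond a fixed cut-off.

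**5. The non-blocked side as comparator.** If later drift multiplies both sides by D and the block multiplies its own side by B, then (B × D)/D = B. This holds if the anaesthetic acts alike on both sides.

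**The case against.** The strongest reply is that *correlation* is a slip. The outcome is called a ratio both times, the Discussion uses the term for a number with a cut-off, and most readers would compute a quotient. The article also condenses a full protocol that is not shown, and the denominator of a secondary variable is often fixed there. The second half of this has weight: the missing baseline is the softer part of the point. The first half explains the error but does not remove it, since the wrong definition stands in both places where the outcome is defined.

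Further, the design does recognise the anaesthetic effect. PI is read on both sides and again once the child is awake, when the Discussion expects the anaesthetic's influence to be gone. That stands, but the PI ratio is a 10-minute quantity taken under anaesthesia, and its definition uses neither safeguard.

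A reader might infer more than the documents support:
- *That the index must be either uninformative or contaminated.* It need not be. A quotient on the post-mask reading is informative, and that reading is planned.
- *That specificity would collapse.* This needs a pre-induction baseline and the adult cut-off of 1.4. No section chooses that baseline or adopts that cut-off for these children. A uniform anaesthetic multiplier would leave ranking within an arm unchanged.
- *That the randomised comparison is biased.* The ratio is secondary, the primary outcome refers to PI values, and how PI behaves under each anaesthetic is part of the question.
- *That injury to the operated limb confounds the ratio.* No section reports an effect of injury on PI, and eligibility is elective upper limb surgery, not injury alone.

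**Conclusion.** The point holds for a secondary outcome. That the definition is wrong follows from the text and needs no assumption: a correlation gives no value per child, is blind to a common multiplicative rise, and does not match the ratio cited in the Discussion.

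That the baseline should be named follows from two pre-block readings with induction between them and the article's statement that both drugs affect PI. A pre-induction denominator would mix the anaesthetic effect with the block effect. By how much cannot be taken from the documents. The simulated figures rest on assumed spreads and multipliers and show direction only; with no anaesthetic effect, the pre-induction baseline does no worse. The sample size is not affected.

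**What to change.** In the abstract and under Secondary outcomes, delete *correlation*. Define the PI ratio for each child and each finger on the blocked side as PI at 10 minutes after the block divided by PI right after the laryngeal mask is placed, the last reading before the block. Report the same ratio on the non-blocked side as comparator, for example as the difference blocked minus non-blocked on the log scale, to account for anaesthetic drift after the post-mask reading. Fix this before the data are analysed.

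The cost is wording: every reading is already scheduled, on both sides and both fingers. There is one small drawback. The Discussion warns that PI may already be near its peak once the anaesthetic's vasodilation is at its height and may not rise further with the block. A post-mask denominator may therefore compress the ratio, and the write-up should say so.
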